## Abstract

**Background:**

Despite showing strong evidence of positive outcomes, a common problem in the field of digital health is poor engagement and adherence. Non–health care, for-profit digital ventures, such as Facebook, LinkedIn, and Twitter, conduct behavioral experiments to increase user engagement. To our knowledge, digital health organizations have not published similar types of experiments in ad libitum environments, and there are limited published data indicating whether nudges and prompts can be leveraged to increase engagement with digital health interventions.

**Objective:**

The main objective of our 3-arm randomized controlled trial is to test whether registered members in two well-established digital health courses for anxiety and depression will engage with four different types of nudges and prompts, and whether engaging with nudges and prompts increases engagement within the courses.

**Methods:**

New members who register for the self-guided anxiety and depression courses on the Evolution Health platform will be randomized into 1 of 3 arms. The first control arm will feature a member home page without any behavioral nudges or prompts. The second arm will feature a member home page with a *Tip-of-the-Day* section containing directive content. Arm 3 will feature a member home page with a *Tip-of-the-Day* section containing social proof and present bias content. The third arm will also feature a to-do item checklist.

**Results:**

The experiment was designed in August 2021 and was launched in November 2021. Initially, we will measure engagement with the tips and the to-do checklist by calculating the frequency of use by age and gender. If members do engage, we will then, according to age and gender, examine whether nudges and prompts result in higher course completion rates and whether specific types of prompts and nudges are more popular than others.

**Conclusions:**

Our 3-arm randomized controlled trial will be the first to compare four distinct types of behavioral prompts and nudges in two self-guided digital health courses that were designed to treat mental health issues. We expect the results to generate insights into which types of behavioral prompts and nudges work best in the population. If they are shown to increase engagement, the insights will then be used to apply prompts and nudges to the platform’s addiction-focused courses. Based on the results of the experiment, the insights will be applied to using artificial intelligence to train the platform to recognize different usage patterns and provide specific engagement recommendations to stratified users.

**International Registered Report Identifier (IRRID):**

DERR1-10.2196/37231

## Introduction

### Background

From its inception in the mid-1990s, digital health promised personalized treatments that patients could access from home. It was anticipated that such treatments would have a broad reach, resulting in improved health outcomes and decreased costs [1-3]. Over the past 2 decades, research examining the efficacy of self-guided digital health interventions has intensified. These studies have shown evidence of efficacy, especially for individuals with mental health concerns [4-6].

Although digital health interventions appear to be effective, patterns that have remained consistent in research are poor adherence and a lack of compliance [7-9]. These patterns were first recognized in 2005 and deemed *The Law of Attrition* [10].

As early as 2009, systematic reviews have identified poor adherence and a lack of compliance as an issue that needs to be addressed [11]. This issue persists in a recent meta-analytic review on digital interventions for depression that illustrate efficacy but highlight compliance as a major challenge [12].

This issue of adherence and compliance is complex and is rooted in a number of systemic and individual factors [13-18]. However, it is an important topic, as evidence indicates that higher levels of engagement are associated with improved health outcomes [19,20].

Digital health interventions are becoming increasingly common and accessible. Patients’ use of and trust in these interventions have been intensified by the COVID-19 pandemic. The use of digital health interventions for mental health concerns is growing [21,22], and there is a shortage of professionals that can meet this growing demand. As such, it is important to determine how to increase engagement in digital health programs to maximize their efficacy.

### Behavioral Economics

Behavioral economics leverages psychological experimentation to develop theories about human decision-making, and this field has identified a range of biases around the way people think and feel [23,24].

The utility of behavioral economics is vast, and digital health has leveraged the discipline, allowing researchers to investigate how people use digital health programs and obtain insights on the characteristics of people who use them. Several digital health studies have investigated the use of several strategies, including the use of cooperative games and incentives [25], gamification [26,27], serious games [28,29], and positive behavioral support [30,31].

### Our Use of Behavioral Economics

In our study, we will be examining the effectiveness of nudge theory and behavioral prompts in two ad libitum, self-guided digital behavior change courses.

#### Nudge Theory

Nudge theory, which was popularized in the 2008 book *Nudge: Improving Decisions About Health, Wealth, and Happiness* [24], leverages indirect, positive suggestions to influence decision-making and behavior.

There is a paucity of quality research that analyzes the use of nudges in digital health. A 2019 scoping review examined the use of nudges in both web-based and real-world physical activity interventions [32]. In the 35 publications reviewed, 8 were web-based studies. The authors concluded that although nudging may be an effective approach to promoting physical activity, there are large gaps in research, and further studies are needed that are explicitly based on nudge insights.

A 2020 editorial in *Personalized Medicine* addressed the meaningful adoption of nudges in digital health [33]. The authors acknowledged that the use of nudges in digital health interventions is rare and advocated for the use of nudges to promote positive behavior change.

#### Behavioral Prompts

In applied behavioral analysis, behavioral prompts are cues that are specifically designed to encourage individuals to perform a specific task [34]. In our study, we will be employing the following two types of behavioral prompts, which are anchored in nudge theory: daily tips and a to-do checklist (Table 1).

Figure 1 is an example of a present bias tip that could randomly appear on a member’s main home page.

**Table 1 table1:** Example nudges and prompts.

Delivery format	Content type	Text example from our study
Tip	Directive content	“Express yourself by uploading your own image!”
Tip	Social proof	“Many members have similar goals as yours. Reviewing other members' goals can help you reach your own.”
Tip	Present bias	“Feel better sooner by learning from others. Read what others have posted on the community.”
Prompt	To-do checklist	“Watch the Getting Started Video”

**Figure 1 figure1:**

Present bias tip.

We have not observed sufficient evidence for determining whether nudges and behavioral prompts can be strategically applied to increase engagement and decrease attrition in courses for depression and anxiety [35]. This is hypothesized in digital health that greater overall engagement may lead to better health outcomes [19,20,36].

Engagement experiments in popular, non–health care digital platforms are common. Although they are scientific in nature, they are not typically published. This makes sense, as they are conducted within private companies and are associated with trade secrets. For example, social network sites, such as Facebook, LinkedIn, and Twitter, generate revenue based on page views and the time users spend on the site. In a 2015 presentation, it was revealed that LinkedIn has over 400 controlled experiments being conducted per day [37]. Similar studies with an ad libitum population are required in digital health, and our study is an attempt to fill this gap.

### Objective

The main objective of our 3-arm randomized controlled trial is to test whether registered members in two well-established, self-guided digital health courses for anxiety and depression will engage with four different types of nudges and prompts, and whether engaging with nudges and prompts increases engagement within the courses.

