### Randomization

During the registration process, by using a random number generator, new members will be assigned into 1 of the 3 arms (Figure 2). Randomization will be conducted by using simple randomization.

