### Intervention Groups

Members allocated to the first arm will be presented with a member home page that contains no behavioral prompts. Figure 3 is a screenshot of an arm 1 homepage for a member who chooses to engage with the depression course.

Members allocated to the second arm will be presented with a member page that contains a *Tip-of-the-Day* section containing directive content. The randomization strategy for the 35 directive tips is randomization without replacement. Figure 4 is a screenshot of an arm 2 homepage for a member who chooses to engage with the depression course.

Members allocated to the third arm will be presented with two sections that contain interactive prompts. The first is a *Tip-of-the-Day* section containing social proof and present bias content. At each log in, members will see a new tip. The randomization strategy for the tips is randomization without replacement. There are 15 social proof tips and 15 present bias tips.

In addition to the tips of the day, the third arm will also feature a to-do checklist that lists interactive course components. When a member clicks on an interactive component, they will be brought to the exercise. When they complete the exercise, the item is marked as complete with a check mark. Figure 5 is a screenshot of an arm 3 homepage for a member who chooses to engage with the depression course.

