### Data Collection

Evolution Health developed a custom data collection interface and reporting mechanism. Data will be collected for each member who is randomized into the experiment. Data on age and gender will be collected at registration or at secure sign-on in various white-label versions. The course components that will be promoted by the tips and to-do items are listed in Table 4.

The following behaviors are tracked in the custom database for each tip and to-do item that is randomly presented to a user: whether a tip was shown, whether a tip was clicked on, and whether a user completed the course component described in a tip or to-do item.

It is possible for a single member to participate in both courses. However, the study was designed to test behavioral economics prompts, not courses. Participants will be randomized to an intervention arm in which behavioral nudges and prompts are consistent across courses.

**Table 4 table4:** Course components tracked for engagement.

Action code	Course component
1^a^	Uploading a personal image to their profile
2^a^	Completing cognitive behavioral therapy session 1
3^a^	Use of the program’s diary
4^a^	Read a community post
5	Review another member’s profile
6	Posting in the community
7^a^	Review a course worksheet
8^a^	Set personal goals
9	Read other members’ goals
10^a^	Complete the depression and anxiety test
11^a^	Watch the *Getting Started* video
12	Give a community member a thumbs-up
13	Encourage a community member by clicking their “show support” icon
14	Private message a community moderator

^a^Item in the to-do checklist.

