### Primary Outcome: Engagement With Tips and To-do Items

We will first measure engagement with the tips and to-do items in arms 2 and 3. We will compare the frequency of engagement with each nudge and behavioral prompt by age and gender. A member’s engagement with tips will be measured as the proportion of tips that were clicked. Specifically, it will be a value between 0 and 1, calculated as the number of tips that a member clicked divided by the number of tips that were presented to the member. Engagement with to-do items will be measured as the number of to-do items that a member clicked, and course component completion rates will be measured as the number of course components that a member completed. All comparisons between arms 2 and 3 will be conducted by using an independent sample 1-tailed *t* test; a conventional α level (.05) for statistical significance will be used.

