### Secondary Outcomes: Completion of Course Components

A secondary outcome of this experiment is to test whether the presentation of tips and to-do items increases the overall completion of course content. We will achieve this by comparing course component completion rates in arm 2 and arm 3 via a 1-way ANOVA in which the types of tips are used as the independent variable. We will then assess if age and gender predict which type of tip is the most engaging by using multiple regression.

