### Strengths and Limitations

A strength of this experiment is that it will be conducted in an ad libitum environment. Unlike most digital health studies, ours will not be conducted with a small population in a controlled environment. Further, members will not be aware of the experiment, which will limit participant bias and the Hawthorne effect.

A limitation of this experiment is that, especially due to the anonymity of members, we have no way of knowing who members are. We have no way of knowing whether registrants are people with depression or anxiety who are seeking help, or are browsing for other reasons. However, we have exceeded sample size requirements and believe that the large number of subjects should dampen these effects on the results.

A final limitation is that not all white-label clients license all course components. For example, some community tools and the depression and anxiety test are feature flags that are not used by all white-label clients. As the primary purpose of this experiment is to test whether members engage with prompts and nudges, we do not expect this particular limitation to hamper the overall results.

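### The main objective asks about the effect of engaging with prompts, which members choose; the trial randomises only the showing of prompts, and the planned completion comparison omits the no-prompt arm

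*Protocol article*

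**What the plan says.** The main objective, worded the same way in the Abstract and in the Introduction under Objective, has two parts. The first is whether members will use the prompts. The second is "whether engaging with nudges and prompts increases engagement within the courses".

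Under Randomization, "new members will be assigned into 1 of the 3 arms"; what differs between arms is the home page. On arm 1, Intervention Groups states: "Members allocated to the first arm will be presented with a member home page that contains no behavioral prompts". Arm 2 shows directive tips. Arm 3 shows social proof and present bias tips plus a to-do checklist.

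Under Primary Outcome, a member's engagement with tips is a proportion, "calculated as the number of tips that a member clicked divided by the number of tips that were presented to the member". Engagement with the checklist is a count of items clicked.

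Under Secondary Outcomes, the aim is to "test whether the presentation of tips and to-do items increases the overall completion of course content". The analysis given is a one-way ANOVA of completion in arms 2 and 3, with tip type as the factor. The tertiary analysis of engagement by tip type also uses arms 2 and 3.

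**The concern.** The objective and the secondary outcome ask different causal questions. One concerns the effect of using prompts, the other the effect of being shown them. Randomisation protects only the second. Use is decided by the member after allocation, in a setting that the article itself describes as free use: "A strength of this experiment is that it will be conducted in an ad libitum environment". Members who are keener to work through a course may plausibly both click more and complete more, whether or not the prompts do anything.

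What is at stake is the claim that the trial may make. With the objective as worded, an association between clicking and completing would appear to answer it, although the association could come from selection alone. The data for such an analysis exist, since the database records "whether a tip was shown, whether a tip was clicked on, and whether a user completed the course component described in a tip". In arm 3 the two measures also overlap by design. For the checklist, "When a member clicks on an interactive component, they will be brought to the exercise", and completion of that exercise is then tracked.

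**Working it through.** The plan gives no figure for this point, so the check is mainly a comparison of sections.

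**What each section asks or fixes**

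| Place in the protocol article | Exposure or contrast | Randomised? |
|---|---|---|
| Abstract and Introduction, Objective | Engaging with prompts | No |
| Randomization; Intervention Groups | Home page version, arms 1 to 3 | Yes |
| Primary Outcome | Clicking, compared between arms 2 and 3 and by age and gender | Arm is; clicking is the outcome |
| Secondary Outcomes | Presentation of prompts; analysed as arm 2 against arm 3 by tip type | Arm is |
| Tertiary Outcomes | Tip type, arms 2 and 3 | Arm is |

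Two things follow.

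1. No listed analysis has engaging as the exposure and course completion as the outcome in a way that identifies a causal effect. Arm 1 members have no prompt to engage with, so within the trial engaging varies only by members' own choice among those shown prompts.
2. Arm 2 against arm 3 contrasts two pages that both carry prompts. If both raised completion over arm 1 by the same amount, the contrast would be zero although showing prompts works. The presentation question needs arm 1.

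**Hypothetical illustration of selection (all inputs assumed, none from the article)**

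Suppose 20% of members are motivated and prompts have no effect. For motivated and other members, let the click probabilities be c1 and c0 and the mean numbers of components completed be m1 and m0.

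Mean in clickers = (0.2·c1·m1 + 0.8·c0·m0) / (0.2·c1 + 0.8·c0)

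Mean in non-clickers = (0.2·(1−c1)·m1 + 0.8·(1−c0)·m0) / (0.2·(1−c1) + 0.8·(1−c0))

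- Strong inputs (c1 = 0.6, c0 = 0.1, m1 = 4, m0 = 0.5): clickers (0.48 + 0.04)/0.20 = 2.60; non-clickers (0.32 + 0.36)/0.80 = 0.85; ratio 3.1.
- Mild inputs (c1 = 0.5, c0 = 0.2, m1 = 2, m0 = 1): clickers 0.36/0.26 = 1.38; non-clickers 0.84/0.74 = 1.14; ratio 1.2.

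The same calculation for a completion proportion, with c1 = 0.4 and c0 = 0.1 (16% click) and 4.5% completing overall:

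- Completion 10% in motivated and 3.125% in other members: clickers (0.008 + 0.0025)/0.16 = 6.6%; non-clickers (0.012 + 0.0225)/0.84 = 4.1%; difference 2.5 points.
- Completion 15% and 1.875%: clickers (0.012 + 0.0015)/0.16 = 8.4%; non-clickers (0.018 + 0.0135)/0.84 = 3.75%; difference 4.7 points.

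For scale, the Power and Sample Size section uses 3.14% and 5.79%, a gap of 2.65 points. These are printed as power but match 16/510 and 28/484, so they are read here as completion proportions.

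In one arm of 1414 members, 0.16 × 1414 ≈ 226 would be clickers. A two-sided test at .05 rejects with probability about Φ((d − 1.96·SE0)/SE1), where d is the difference, SE0 the pooled and SE1 the unpooled standard error:

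- First case: (0.0246 − 1.96 × 0.0150)/0.0174 = −0.28, about 39%.
- Second case: (0.0469 − 1.96 × 0.0150)/0.0193 = 0.90, about 82%.

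**The case against.** The strongest reply is that the objective is one loosely worded sentence, printed twice, and that the rest of the article shows what was meant. The Abstract's Results paragraph, the Behavioral Prompts section and Future Directions all ask whether prompts, as an intervention, raise engagement or completion. Secondary Outcomes already speaks of presentation. This is fair and makes the repair easy. It does not remove the conflict, because the sentence at issue is the stated main objective.

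A reader might infer more than the article supports, in four ways:

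- **That a comparison of clickers with non-clickers is planned.** It is not. Every listed comparison is between arms 2 and 3, by tip type, or by age and gender. The warning is conditional.
- **That an association between clicking and completing must be positive even if prompts do nothing.** That depends on motivated members both clicking and completing more. This is plausible but assumed.
- **That the figures above measure a bias in this trial.** They do not. The ratio moves from 3.1 to 1.2 with the inputs.
- **That click and completion are one act throughout.** The direct route from click to exercise is described only for the arm 3 checklist, not for tips, and leading the member to the exercise is the intended mechanism.

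It may also be said that an effect of engaging could be recovered by an instrumental-variable analysis with allocation against arm 1 as the instrument. None is stated. It would need prompts to act only through clicks, which is doubtful because a tip can be read and acted on without a click.

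**Conclusion.** The point holds as a mismatch between the objective, the randomised contrast and the stated analyses. The main objective names a self-selected behaviour after randomisation, the secondary outcome names the randomised exposure, and no analysis in the outcome sections identifies an effect of engaging. The stated completion analysis would not answer the presentation question against no prompts either, because it leaves out arm 1. These conclusions rest on the article's text alone and need no numerical assumption.

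The size of any resulting error cannot be derived from the article. The illustration shows only that selection could produce a gap as large as the difference used for planning. The matter should be corrected because it decides what the trial may conclude. It does not invalidate the randomised data.

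**What to change.** 1. In the Abstract and the Introduction, reword the second part of the main objective to ask whether being shown nudges and prompts, by randomised arm, increases course engagement.
2. In Secondary Outcomes, compare course component completion in arms 2 and 3 with arm 1, for all members as randomised. Count completion in the same way in every arm, whether or not a prompt led to it. Data Collection says that data are collected for each randomised member, and an arm 1 figure appears in the sample size section, so this looks feasible.
3. Add one sentence: any analysis relating clicks to completion is descriptive and gives no evidence of effect.

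The cost is a reworded sentence in two places, a completion comparison that includes arm 1, and one added sentence. The trial would claim an effect of offering prompts, not of using them. The Results section reports that data collection ended in May 2022, so the change cannot alter conduct. It should be dated and described as a clarification of analysis and reporting.

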## Methods

### Digital Health Platform

The digital health platform that will be used in the study is managed by Evolution Health—an evidence-based digital health content provider that features courses based on behavior change techniques, including cognitive behavioral therapy, stages of change, structured relapse prevention, harm reduction, and quizzes based on brief intervention.

The platform offers interactive courses and quizzes for mental health issues, addiction issues, and obesity. The platform contains a moderated community that is based on social cognitive theory.

Memberships are available to individuals who register through the organization’s free-to-consumer program, as well as white-label versions that are licensed by employers, insurance companies, employee assistance programs, educational institutions, nonprofit organizations, for-profit health care organizations, and individual therapists.

